## Abstract

**Background:**

Acupuncture is safe and effective for reducing the symptoms of knee osteoarthritis (KOA), but the underlying mechanisms of acupuncture for treating KOA are not fully understood.

**Methods/design:**

In total, 108 participants diagnosed with KOA will be recruited. They will be blinded to group assignment and randomized to either verum acupuncture, sham acupuncture or waiting-list groups with 36 patients in each group. Each patient in the acupuncture group will receive five treatments per week for 2 weeks. This study will focus on detecting the cerebral functional connectivity changes elicited by acupuncture treatment. The Visual Analog Scale and the short form of the McGill Pain Questionnaire, the Western Ontario and McMaster Universities Osteoarthritis Index, the Attention Test Scale, the Pain Assessment of Sphygmomanometer and the 12-Item Short Form Health Survey will be used to evaluate the symptoms and quality of life improvement at the baseline and the end of treatment. The Self-rating Anxiety Scale and the Self-rating Depression Scale will be used at the baseline and the end of treatment to investigate the influence of emotional state on brain activity and clinical variable. To ensure the consistency of acupuncture manipulation, the *deqi* scale will be performed after each acupuncture treatment. During the procedure of outcome evaluation and data analysis, the evaluators and statisticians will be blinded to the group allocation. The repeated measures analysis of variance (3 groups × 2 time points ANOVA) will be employed to analyze numerical variables of the clinical and neuroimaging data generated in the study, then the *t* test will be used in the post-hoc analysis.

**Discussion:**

The results of this randomized, sham- and waiting-list-controlled functional magnetic resonance imaging (fMRI) study will help to investigate the influence of verum acupuncture treatment on the brain activities of patients with KOA, which might provide evidence for the clinical application of verum acupuncture for KOA management.

**Trial registration:**

Chinese Clinical Trial Registry, ID: ChiCT-IOR-17012364. Registered on 14 August 2017.

## Background

Knee osteoarthritis (KOA) is characterized by the degeneration of cartilage in the knee, manifesting as knee pain, function limitation and so forth [1]. As a high-prevalence chronic joint disease [2], KOA has become one of the leading causes of disability in the world and brings an increasing social and economic burden [3, 4]. Furthermore, the pharmacological treatment of KOA, such as the first-line treatment NSAIDs (non-steroidal anti-inflammatory drugs), is unsatisfactory with significant side effects [5].

In China and some other Asian countries, the history of using acupuncture for treating knee pain caused by osteoarthritis can be dated back thousands of years. In Western countries, acupuncture has been gradually accepted as a promising treatment option for KOA. Recently, both clinical studies and systematic reviews have shown that acupuncture is safe and effective for KOA in pain relief [6–8], stiffness [9] and physical function improvement [10] with a low risk of adverse reactions. Although one study has reported that acupuncture can alleviate weight-bearing problems [11], it is considered more economical for improving quality-adjusted life years in the treatment of KOA, compared with NSAIDs [12]. However, the underlying mechanisms of acupuncture for treating KOA remains unclear, which prevents its wider application in clinical practice.

KOA is a complex, chronic pain condition partly due to both nociceptive and neuropathic mechanisms [13]. Previous studies have demonstrated that central sensitization, a pathological change in the central nervous system, plays an important role in the pathogenesis of KOA [14, 15]. With the widely application of neuroimaging techniques in pain research, investigators not only mapped the brain regions which are involved in the central pathogenesis of chronic pain, but also partly explored the central mechanism of acupuncture-induced analgesia by detecting the cerebral responses elicited by acupuncture. Using resting-state functional magnetic resonance imaging (rs-fMRI), researchers found that the patients with chronic pain demonstrated altered functional connectivity (FC) of the medial prefrontal default-mode network (DMN) and a changed regional homogeneity (ReHo) value of the anterior cingulate cortex (ACC) [16–18]. These results greatly enhanced the understanding of the central mechanism of chronic pain and have provided an approach to investigating the mechanism of acupuncture-induced analgesia. For instance, a functional magnetic resonance imaging (fMRI) study has shown that acupuncture can regulate the descending pain-modulatory system of KOA patients by enhancing the FC between the right frontoparietal network (rFPN) and the medial prefrontal cortex (mPFC) [19]. However, the sample size (only 10 in each group) and the dosage of acupuncture treatment (six acupuncture treatments for 4 weeks) of that study were relatively small, and the self-healing tendency of KOA patients could not be excluded due to the lack of waiting-list control.

So, this study aims to (1) investigate the influence of verum acupuncture treatment on the brain activities of patients with KOA compared with that of sham acupuncture treatment and waiting list patients by using fMRI with a larger sample size (36 patients in each group) and (2) analyze the possible correlations between the changes of cerebral activity and the improvement of clinical variables in each group, so as to explore how acupuncture manages pain by modulating brain function.

## Methods/design

### Study design

This is a randomized controlled, parallel neuroimaging study, with participants and assessor blinded to the group assignment. A total of 108 participants diagnosed with KOA in accordance with American College of Rheumatology (ACR) criteria (1991 revised version) [20] will be considered as eligible patients. They will be randomly allocated into three equal groups with 36 patients in each group, including a verum acupuncture group, a sham acupuncture group and a waiting-list group. The treatment period will last for 2 weeks. Outcome measurements and MRI scan will be assessed at baseline and at the end of treatment (Figs. 1 and 2). The changes of clinical variables and cerebral activity of each group will be analyzed after data collection.

**Fig. 1 Fig1:**
[figure not shown]
Flow chart of the trial. The present study is a randomized controlled neuroimaging trial. One hundred and eight knee osteoarthritis (KOA) patients will be included and randomized equally to one of three groups: a verum acupuncture group, a sham acupuncture group and a waiting-list group. For the 36 patients in each group, this trial will include a 2-week baseline period and a 2-week treatment period. During the 2-week treatment, patients in the two acupuncture groups will receive 10 sessions of puncturing treatments, while the waiting-list group will not receive acupuncture. Both the outcome assessments and functional magnetic resonance imaging (fMRI) scan will be performed at two time points: baseline and end of acupuncture treatments. The central mechanism of verum acupuncture in the treatment of KOA will be analyzed after data collection

**Fig. 2 Fig2:**
[figure not shown]
Study schedule for data collection. The informed consent and examination will be conducted after recruitment. Then, matched KOA patients will be randomized into three groups, only two acupuncture groups will receive treatment. Both clinical outcomes and functional magnetic resonance imaging (fMRI) scans will be performed at two time points including: the baseline and the end of acupuncture treatments. Adverse events will be recorded in the case report form at any time during the study. *VAS* Visual Analogue Score, *MPQ* McGill Pain Questionnaire, *WOMAC* Western Ontario and McMaster University Osteoarthritis Index, *ATS* Attention Test Scale, *PAS* Pain Assessment of Sphygmomanometer, *SAS* Self-Rating Anxiety Scale, *SDS* Self-Rating Depression Scale, *SF-12* Short Form 12 Health Survey

#### Sample size

In general, 12 to 15 patients per group provided statistical power in MRI studies [21]. According to our previous studies, 25 patients in each group has a more stable statistical power for brain functional network analysis [22]. In order to have a powerful and repeatable statistical power, we require 30 patients per group in this trial. Considering a 20% dropout rate and the possible excessive head motion during scanning, we will include 36 KOA participants in each group. Finally, we plan to enroll 108 participants and each group will undergo two MRI scans to investigate the different central responses among verum acupuncture, sham acupuncture and waiting-list treatment in KOA patients with pain.

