#### Randomization

Eligible patients will be randomized in a ratio of 1:1:1 to the verum acupuncture group, sham acupuncture group and waiting-list group with 36 patients in each group using simple randomization. Random number lists will be created in accordance with PROC PLAN of SAS 9.2 (SAS Institute Inc., Cary, NC, USA). The randomization allocation will use sequentially numbered, opaque and sealed envelopes by an independent assistant.

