### Outcome measurement

The clinical outcome will measure patients’ knee pain and physical function, quality of life (QOL) and emotional status. All measurement will be performed at the baseline and at the end of the treatment. The primary outcome measurements are the Visual Analog Scale (VAS)[25] and short-form of the McGill Pain Questionnaire (SF-MPQ) [26]. The VAS is a 10-point scale selected to quantitatively evaluate the level of knee pain during the study. It scores from “0 (none),” “about 2 (mild),” “around 5 (moderate),” “almost 8 (severe),” and “nearly 10 (unbearable)” spaced along the continuum. The SF-MPQ focuses on evaluating the sensory and affective components of knee pain in the last 2 weeks. It mainly consists of 15 descriptors (11 sensory and four affective) rating on an intensity scale as “0 = none,” “2 = moderate,” and “3 = severe.” A higher total score indicates more severe pain.

The secondary outcomes are the Western Ontario and McMaster Universities Osteoarthritis Index (WOMAC) [27], the Attention Test Scale (ATS), the Pain Assessment of Sphygmomanometer (PAS) [28] and the 12-Item Short Form Health Survey (SF-12) [29]. The WOMAC is a self-administered questionnaire consisting of 24 items divided into three subscales: pain (five items), stiffness (two items) and physical function (17 items). These measurements will be used to subsidiarily evaluate the symptom and QOL improvement at the baseline and the end of treatment.

Furthermore, to investigate the influence of emotional state on the brain activity, the Self-rating Anxiety Scale (SAS) [30] and the Self-rating Depression Scale (SDS) [31] will be used at the baseline and the end of treatment. To ensure the consistency of acupuncture manipulation, the *deqi* scale will be performed after each acupuncture treatment (Fig. 2). The *deqi* scale is derived from the Chinese version of the modified Massachusetts General Hospital Acupuncture Sensation Scale (C-MASS) [32, 33], the validity and reliability of which have been tested [33, 34]. The scale will be used to evaluate the needle sensations (including soreness, numbness, fullness, heaviness, aching), respectively. All the evaluations are evaluated by two trained, licensed physicians.

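### The enrolment of 36 per group inflates 30 by multiplying by 1.2; at the stated 20% loss it leaves an expected 28.8 per group, not 30

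*Protocol article*

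**What the plan says.** The Sample size section of the protocol article builds up its number in steps. It cites 12 to 15 patients per group as usual in MRI studies, then 25 per group as more stable for brain network analysis, and then sets its own target and names two reasons for enrolling more than that: "we require 30 patients per group in this trial. Considering a 20% dropout rate and the possible excessive head motion during scanning". The result is "we will include 36 KOA participants in each group", and for the trial as a whole "we plan to enroll 108 participants and each group will undergo two MRI scans".

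The Randomization section confirms equal allocation: "Eligible patients will be randomized in a ratio of 1:1:1". The figure of 36 per group recurs in the Abstract, Background, Study design, Fig. 1 legend and Discussion. No rate is given for scans lost to head motion, and nothing in the article says that patients who drop out will be replaced.

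**The concern.** The target, the loss rate and the enrolment stand next to each other in one paragraph, so a reader can check them, and they do not agree. Adding 20% to the target is a common slip. The dropout rate applies to the patients enrolled, not to the patients wanted at the end, so the target has to be divided by the share retained.

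What is at stake is the number of patients with usable data. The section ties its expectation of powerful and repeatable results to 30 per group, and the larger sample is offered in the Background and Discussion as an advance over an earlier study with 10 per group. The 30 is the only sample-size target in the article that can be checked, and the article's own loss rate does not deliver it.

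**Working it through.** **Inputs** (all from Sample size, except the allocation, which is from Randomization)
- Required per group: 30
- Dropout rate: 20%
- Loss to head motion: named, no rate given
- Enrolled per group: 36; total: 108; allocation 1:1:1

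**Reproducing the plan's figure**
- Target × (1 + dropout) = 30 × 1.20 = 36 per group; 3 × 36 = 108. This matches the article exactly.

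**Correct inflation**
- Target / (1 − dropout) = 30 / 0.80 = 37.5, rounded up to 38 per group; 3 × 38 = 114.

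**What 36 delivers**
- Expected number retained: 36 × 0.80 = 28.8 per group, against 30. Shortfall: 30 − 28.8 = 1.2 per group.
- Over the trial: 108 × 0.80 = 86.4, against 90.
- Largest loss that still leaves 30: 36 − 30 = 6 patients, 6/36 = 16.7%, from all causes together.
- If each patient is lost independently with probability 0.20, the chance that a given group keeps at least 30 of 36 is 0.40. For all three groups it is 0.401³ = 0.064.

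**The two readings of head motion**
- The 20% covers dropout and unusable scans together: expected 28.8 per group, still below 30.
- Head motion is a further loss: 28.8 × (1 − m), where m is the share of completers with unusable scans. The article gives no m. Purely as an illustration, m = 5%, 10% or 15% gives 27.4, 25.9 or 24.5 per group.

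**How much it matters**
- The article states no effect size, standard deviation or power for the 30, so the effect on its own power claim cannot be calculated. As a yardstick only, take a two-sample t test, two-sided 0.05, 80% power. The detectable difference is 0.736 SD at 30 per group and 0.751 SD at 28.8. For a difference of 0.736 SD, power falls from 80.0% to 78.4%.

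**The case against.** The strongest reply is that nothing of substance turns on this. The 30 is reached by rule of thumb, so falling to 28.8 crosses no calculated boundary, and 28.8 is still above the 25 per group that the section itself calls more stable. The yardstick above moves very little. All of this stands, and it limits how serious the point is.

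A second reply is that actual losses look lower. The Trial status section reports 89 recruited and 80 who completed the intervention, so non-completion was at most 9/89, about 10%, and some of the nine may still have been in treatment. At 10% loss, 36 × 0.90 = 32.4 per group; under the same independence assumption, the chance of keeping at least 30 is 94% in one group and 82% in all three. This also stands as a statement about practical risk, although it says nothing about scans excluded for motion. Better retention later does not make the planning figure correct.

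Three stronger readings are tempting, and the documents do not support them:
- A reader might infer that head motion certainly has no allowance. That follows only if "the possible excessive head motion during scanning" is a loss separate from the 20%. It is the more literal reading, but a single combined 20% is possible.
- A reader might infer that the groups have almost no chance of reaching 30. Such a figure needs a motion-loss rate that the article does not give.
- A reader might infer that the trial is sized on the wrong outcome, since "The primary outcome measurements are the Visual Analog Scale" and the short-form McGill Pain Questionnaire, whereas the 30 comes from imaging experience. That is a separate question from the inflation. The aims stated in the Background concern brain activity and its correlation with clinical change, so sizing on imaging is consistent with them.

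**Conclusion.** The sample-size paragraph is wrong as written. Its 36 comes from 30 × 1.20, where 30/0.80 = 37.5 was needed. This conclusion uses only the article's own figures and survives either reading of head motion. It assumes that dropouts are not replaced, which matches the article's silence on replacement. Intention-to-treat analysis of available data, as stated under Data analysis, does not restore a missing or unusable scan.

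The consequence is minor. The 0.40 and 0.064 hold only if true loss is 20% and independent between patients. Any further shortfall from head motion cannot be quantified from the article. The error does not show that the trial is underpowered, because no power was calculated for 30 in the first place.

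**What to change.** Keep 108 patients and reword the paragraph in one of two ways:
- with 36 per group and 20% total loss, about 28–29 evaluable patients per group are expected; or
- total loss, including unusable scans, must not exceed 16.7% to keep 30 per group.

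In either case, state whether the 20% includes scans lost to head motion. If it does not, give the assumed motion loss separately.

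The cost is a few sentences and a slightly less favourable stated number. No extra patients and no change to allocation or analysis are needed. Holding to 30 per group at 20% loss would instead take 38 per group, 114 in total, which is 6 more patients. The small size of the shortfall does not call for that.

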#### Randomization

Eligible patients will be randomized in a ratio of 1:1:1 to the verum acupuncture group, sham acupuncture group and waiting-list group with 36 patients in each group using simple randomization. Random number lists will be created in accordance with PROC PLAN of SAS 9.2 (SAS Institute Inc., Cary, NC, USA). The randomization allocation will use sequentially numbered, opaque and sealed envelopes by an independent assistant.

#### Blinding

Acupuncturists, who will be asked to apply the same method of stimulation, will not be blinded to treatment allocation for the different location in each group. And the acupuncture treatment will be revealed to the acupuncturists before treatment starts. However, participants will be blinded to group assignment. They will be informed that there are two types of acupuncture treatment provided in this study. They will accept one of them in a separate compartment. Each of the patients only knows the type which they accepted but not the other type. As the waiting-list group is without any intervention, it is impossible to blind the patients, clinicians and investigators. The evaluators and statisticians will be blinded to the group allocation in the outcome evaluation procedure and data analysis for the sake of reducing the risk of bias.

### Participants

Knee-pain patients who suffered from KOA according to the American College of Rheumatology (ACR) criteria (1991 revised version) [20] will be recruited from outpatient and inpatient departments of the First Affiliated Hospital and the Third Affiliated Hospital of Chengdu University of Traditional Chinese Medicine. Potential patients will also be recruited through posters, the Internet and leaflets.

#### Inclusion criteria

Inclusion criteria require that all patients: (1) meet the diagnostic criteria for KOA set by the ACR in 1991 [20], including retropatellar, medial or lateral KOA, etc., with no traumatic aetiology, (2) are aged between 40 and 60 years and right-handed, (3) have not taken any pain-killing medicine within 1 month, (4) have not received any acupuncture treatment within 1 month, (5) have had at least 3 months of knee-pain duration and (6) have an average knee-pain score on a Visual Analog Scale (VAS) ≥ 3 (range from 0 to 10) in the past 2 weeks, (7) have I–II degree knee-joint radiological change on the Kellgren-Lawrence scale and (8) have signed an informed consent.

#### Exclusion criteria

Patients will be excluded if they: (1) are alcohol or drug abusers or are taking other medications that may influence brain-imaging outcomes or (2) are pregnant or lactating women or (3) are suffering from psychiatric, neurological, gastrointestinal, cardiovascular, infectious, immunological, respiratory or renal illnesses or (4) are suffering from any other chronic pain condition or have a history of head trauma with loss of consciousness or (5) are diagnosed as rheumatoid arthritis or other leg-related pain disorders or (6) have MRI contraindications such as claustrophobia, cardiac pacemaker, defibrillator, heart stenting, intrauterine device or (7) have acupuncture contraindications such as a bleeding tendency.

#### Informed consent

The authors retain full control of the manuscript content. All patients will be informed of the random allocation of verum acupuncture, sham acupuncture or waiting-list treatment and the possible benefits and risks. They will voluntarily sign the informed consent before enrollment. The patients will be free to withdraw from the study at any time without a specific reason and without any penalty or loss of benefits. However, we will attempt to record the reason for withdrawal and encourage the participant to remain in the study if possible.

### Interventions

Both ancient literature and previous clinical studies have provided the validated and reliable acupuncture procedure for treating knee pain. Acupuncture treatment will be performed in different compartments by two study-trained, licensed acupuncturists who have more than 6 years of acupuncture clinical practice experience.

#### Verum acupuncture group

The selected acupoints for the verum acupuncture treatment include GB34 (*yanglingquan*), SP9 (*yinlingquan*) and two *ashi* points. An *ashi* point is the position where there is a sensation of acid, distension and pain around the knee joint. KOA’s *ashi* point is a temporary acupoint which can appear anywhere in the knee joints. If there is no *ashi* point, EX-LE04 (*neixiyan*) and EX-LE5 (*waixiiyan*) will be selected for *ashi*- point replacement (Fig. 3). If the KOA patients have unilateral knee pain, points on the painful knee will be selected. If the KOA patients have bilateral knee pain, points on both knees will be selected.

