### Data analysis

Before the data analyses, the research group will provide a statistical scheme to the statisticians. The scheme will include the required data and processing method. The data analysis process according to the scheme will be completed by statisticians who are independent from the research team and blinded to the test settings.

For the clinical data, statistical analyses will be performed with SPSS 22.0 statistics software (IBM Corp, Armonk, NY, USA). For the fMRI data, preprocessing and functional connectivity analysis will be performed by SPM12 software (SPM12, Wellcome Department of Imaging Neuroscience, London, UK; http://www.fil.ion.ucl.ac.uk/spm/) performing on MATLAB 8.6 (Mathworks, Inc., Natick, MA, USA) .

Both between and within groups, the numerical variables include the clinical data collected from the VAS, the short form of the McGill Pain Questionnaire, the WOMAC, ATS, SAS, SDS, PAS, *deqi* scale and the SF-12 scale, and Fisher’s transformed z value by functional connectivity analysis on neuroimaging data. Since there are three groups (verum acupuncture group, sham acupuncture group and waiting-list group) with two time points (pre-treatment and post-treatment), the repeated measures analysis of variance (ANOVA) will be employed to analyze both the clinical and neuroimaging data generated by the present study design. In the 2 × 3 group factorial design, the dependent variables were the clinical/neuroimaging data collected from pre-treatment and post-treatment, and data in the three different conditions (groups) will serve as the independent variable. Then, *t* tests will be used in the post-hoc analysis. The chi-square test will be used for categorical variables. All data are presented as the mean ± standard deviation (SD). Data are analyzed following intention to treat. A two-sided test is applied for available data and *P* < 0.05 is considered statistically significant. Finally, the Pearson’s correlation between the changes of cerebral activity and the improvement of clinical variables will be performed in each group.

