### The reason of acupoint/non-acupoint selection

According to the theory of traditional Chinese acupuncture, all the points can treat the disease of the local area and adjacent area. In this study, four local acupoints are selected in the verum acupuncture group, including GB34 (*yanglingquan*), SP9 (*yinlingquan*) and two *ashi* acupoints around the knee joint. GB34, the *He-sea* point and lower *He-sea* point of the Gallbladder Meridian of Foot-*Shaoyang*, is located on the lateral side of the calf and in the depression below the front of the fibular head. GB34 is also known as the converging point of the tendons and is usually used for knee-pain treatment. SP9 is the *He-sea* point of the Spleen Meridian of Foot-*Taiyin*. It is located on the medial side of the leg, and in the depression between the medial tibial medial margin and the medial tibial margin. It is one of the most commonly used points for the treatment of knee joint diseases. *Ashi* acupoints are the pain spots or the tender points which are good for alleviating local pain. If there is no *ashi* acupoint reported, EX-LE04 and EX-LE05 will be selected as a replacement for the *ashi* acupoints. Briefly, GB34, SP9, *ashi* points, EX-LE04 and EX-LE05, which are also used in many other acupuncture-treating KOA RCTs [35–37], are commonly used for KOA treatment in the acupuncture clinic (Fig. 3). A clinical study has used these acupoints/non-acupoints and shown that the therapeutic effect of acupuncture plus medication is superior to that of simple medication. The results demonstrated that acupuncture is effective in improving KOA patients’ pain severity and other symptoms [38].

The four non-acupoints in the sham acupuncture group are also selected around the knee joint (NP-1, NP-2, NP-3 and NP-4). These non-acupoints are beside the verum acupoints and not on any regular meridians, which could maximally help to blind the patients and exclude the bias of the spinal segmental effect of the acupoints (Figs. 4 and 5).

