### Quality control is the precondition for the reliability of results

To improve the result reliability of this study, we designed the quality control program from the following aspects: (1) baseline homogeneity: patient selection for the influence of age and handedness on cerebral function and structure have long been investigated, this study restricts the participants to age between 40 to 60 years and to being right-handed; (2) acupuncture manipulation: in this study, all researchers will be trained to well understand the design and process of the trial, the use of the CRF, as well as measurements of quality. To avoid the manipulation difference, two veteran acupuncturists, who received special and standardized training before the trial, carry out all the treatment with the standard operation procedure. In addition, superfluous communication between acupuncturists and patients during acupuncture is forbidden. Besides, trained outcome assessors will be blinded to group allocation and responsible for the outcome assessment; (3) fMRI scan: to ensure the stability of MRI data acquisition, only one technician will perform all scans in the same MRI machine according to the related operation standard and the design of the study in the fixed condition. Furthermore, the unified guidebook will be used to standardize the opinions and behaviors of the researchers. Moreover, during the 24 h before scanning, participants will be asked to maintain their regular lifestyle and avoid overexertion and staying up late. The use of alcohol, tobacco, tea and coffee is prohibited. Before being scanned, the emotional state of each participant will be evaluated via the emotional state assessment scales. During the scan, participants will be asked to close their eyes and use a blindfold and to plug their ears with earplugs, stay awake and not speak; (4) *deqi*: considering the importance of the *deqi* sensation for the acupuncture effect, the needle sensation scale (*deqi* scale) will be measured after each treatment to evaluate the stimuli and *deqi* sensation in the process, which will help to exclude the bias of *deqi*.

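### Pain side sets needle number and site, but the stated analysis ignores it, leaving the within-arm brain–symptom correlations open to confounding by unilateral versus bilateral pain

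*Protocol article*

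**What the plan says.** Eligibility does not depend on the side of pain. Under Inclusion criteria, patients must "meet the diagnostic criteria for KOA set by the ACR in 1991 [20], including retropatellar, medial or lateral KOA, etc., with no traumatic aetiology", with no condition on left, right or both knees.

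Side does determine treatment. Under Verum acupuncture group: "If the KOA patients have unilateral knee pain, points on the painful knee will be selected"; and "If the KOA patients have bilateral knee pain, points on both knees will be selected". The Discussion section on acupoint selection says that "four local acupoints are selected in the verum acupuncture group": GB34, SP9 and two ashi points, or their two replacements. The Sham acupuncture group section names four non-acupoints and says that the procedure is that of the verum arm. It does not restate the side rule, so needling of both knees in bilateral sham patients is an inference. The waiting-list group receives no needling in the two weeks.

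Randomization is simple, 1:1:1, with no strata. Data analysis describes a repeated measures ANOVA of three groups by two times, in which "data in the three different conditions (groups) will serve as the independent variable", followed by t tests. Pearson correlations between brain change and clinical change are then computed in each group, with no adjustment named. These correlations serve the second of the two aims stated at the end of the Background.

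**The concern.** Within an arm, a bilateral patient differs from a unilateral one in two ways at once: the pain comes from two knees, and in the acupuncture arms the needles go to two knees and are more numerous. Either could shift both the change in connectivity and the change in symptoms.

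The comparison of arms is protected by randomization, apart from chance imbalance and extra variance. The correlations are not, because nobody is randomized to a level of brain change or symptom change. If bilateral patients change more, or less, on both measures, a correlation appears in the arm even when the two changes are unrelated among patients with the same side of pain. It would then be read as evidence of how acupuncture relieves pain through the brain, which is the mechanistic conclusion the trial is designed to reach.

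**Working it through.** **Arm sizes.** Sample size requires 30 per group and allows 20% for dropout: 30 × 1.20 = 36, and 3 × 36 = 108. Both stated figures are reproduced. They are used here only as arm sizes; the document gives no effect size, SD or power.

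**Needle number.** Four points per knee and ten sessions (five per week for two weeks):
- Unilateral: 4 per session, 4 × 10 = 40 over the course.
- Bilateral, two ashi points per knee: 8 per session, 80 over the course (ratio 2.0).
- Bilateral, two ashi points in all: 2 × 2 + 2 = 6 per session, 60 over the course (ratio 1.5).

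The wording about points on both knees favours eight, but does not exclude six.

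**Spread within a needled arm.** The bilateral share p is not in the document; assume 30%, 50% or 70%. With 4 versus 8 needles, the mean is 4(1 − p) + 8p and the SD is 4√(p(1 − p)):
- p = 0.3: mean 5.2, SD 1.83 (CV 35%).
- p = 0.5: mean 6.0, SD 2.00 (CV 33%).
- p = 0.7: mean 6.8, SD 1.83 (CV 27%).

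**Chance imbalance between two given arms.** The SD of the difference in bilateral share is √(2p(1 − p)/n). At n = 36 and p = 0.5 this is √(2 × 0.25/36) = 0.118; at p = 0.3 or 0.7 it is 0.108. Exact binomial probabilities of a gap of 20 points or more:
- 36 per arm: 5.3%, 7.6% and 5.3% at p = 0.3, 0.5 and 0.7.
- 30 per arm: 12.0%, 15.5% and 12.0%.

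Part of the step between 36 and 30 is discreteness: 20 points is exactly 6 of 30 patients, but 7.2 of 36, so 8 are needed.

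**Within-arm correlation.** Let bilateral patients differ from unilateral ones by δ₁ in mean brain change and by δ₂ in mean symptom change, and let the two changes be unrelated among patients with the same side of pain. Their covariance in the pooled arm is then p(1 − p)δ₁δ₂. The factor p(1 − p) is 0.3 × 0.7 = 0.21 or 0.5 × 0.5 = 0.25 over the assumed range, so the covariance is zero only if δ₁ or δ₂ is zero. A correlation adjusted for side removes this term. The document gives nothing from which δ₁ or δ₂ could be estimated, so the size of the resulting correlation is unknown.

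**Cell sizes.** With 30 analysed per arm and left and right equally common, each unilateral side has 30(1 − p)/2 patients per arm: 10.5, 7.5 and 4.5 at p = 0.3, 0.5 and 0.7. The bilateral cell has 30p: 9, 15 and 21.

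**The case against.** The strongest reply is that the article condenses a fuller plan. Data analysis mentions a separate scheme given to the statisticians, which may include side. That limits the point to the model as written. But the article does state its between-patient factor and its correlation method, and neither accounts for an attribute that changes the treatment received.

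Several stronger readings are tempting, and the documents do not support them:
- *A contradiction with the handedness rule.* The quality-control section says that "this study restricts the participants to age between 40 to 60 years and to being right-handed". It promises homogeneity of age and handedness and says nothing about pain side. Treating the painful knee or knees is a clear rule and conflicts with nothing.
- *Left- and right-sided effects cancelling in the brain maps.* Nothing in the document shows that the connectivity of interest depends on the painful side, and no lateralised hypothesis is stated. A side term would not undo such cancelling anyway, since the group effect would still be averaged over sides.
- *Systematic bias between arms.* Side is a baseline attribute, balanced in expectation, and a large chance gap is uncommon at 36 per arm.
- *VAS ratings that switch knees.* Patients must "have an average knee-pain score on a Visual Analog Scale (VAS) ≥ 3 (range from 0 to 10") and later rate knee pain, with no knee named at either point. A reader might infer that a bilateral patient could qualify on one knee and rate the other. The text can equally mean one overall rating, made the same way at both visits.

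**Conclusion.** The point stands as a weakness of the stated analysis, mainly for the second aim. Needle number differs within each needled arm by a factor of 2.0, or 1.5 on the narrower reading of the ashi points. For the sham arm this rests on reading the same procedure as including the side rule. In the waiting-list arm only the pain input differs. The unadjusted within-arm correlations can therefore partly reflect bilateral versus unilateral status, and randomization does not prevent this.

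For the arm comparisons the consequence is small: extra variance, and a probability of about 5–8% of a 20-point gap in bilateral share between two given arms at 36 per arm, or 12–16% at 30. Both ranges assume a bilateral share of 30–70%. No view is taken on the needling rule.

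**What to change.** Four changes, all before the analysis:
- Take pain side (left, right, bilateral) from baseline or treatment records for every participant. The site needs it to place needles, so it should be recoverable in the acupuncture arms; waiting-list patients may need their clinical records checked.
- Include side with its interaction with time in the clinical and connectivity models. A side main effect alone would not touch the group-by-time test. With two time points the interaction is the same as side as a covariate for change.
- Use correlations adjusted for side in each group.
- Report side by arm.

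The cost is two degrees of freedom for three categories, or one if only unilateral and bilateral are distinguished. Analyses by side should be labelled descriptive, because the cells are small.

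The VAS entry criterion and outcome definition should not change now. Trial status reports 89 of 108 recruited and 80 finished, so a new index-knee rule would reach about 108 − 89 = 19 participants and give a primary outcome two definitions. It is enough to document which knee the existing ratings refer to, where this is known.
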